#### CostCOM

3.7.3

Patients will receive the CostCOM intervention, which is informed by our prior work [22,42] within 4 weeks of enrollment. CostCOM consists of two interactive one-on-one sessions that last up to 1 h in duration. Sessions take place by phone or video at enrollment and 3 months post-randomization with a remote centralized financial navigator using a commercially available price estimator tool and financial navigation platform (TailorMed Inc, New York, NY). TailorMed is a healthcare technology platform that generates OOPC estimates for systemic therapy using patients’ insurance information, and identifies financial assistance programs for which a patient may be eligible for. During these sessions, patients will receive (1) OOPC communication, a review of insurance benefits and education of the patient-specific OOPC estimate for anticipated systemic treatment regimen obtained using the price estimator tool; (2) Financial navigation: real-time professional guidance to identify financial assistance programs (e.g., co-pay, living expenses) that alleviate costs of care using the financial navigation platform as well as discussion of strategies to improve insurance coverage; and (3) Financial counseling to address the range of patients' financial concerns and enroll patients in financial assistance programs. At the end of each session, the financial navigator will generate a report with data on information discussed, patient enrollments in assistance programs, and the monetary amount of assistance. This data will be shared with the patient.

### Follow-up surveys

3.8

All patients will be surveyed at 3- and 6-months post-randomization to assess patient-reported receipt of cancer supportive services as part of usual care, cost-related cancer care nonadherence [34], material hardship [34], financial worry [31,32], QOL [35], health insurance literacy [43], subjective sleep quality [37], and patients’ experience with the CostCOM and FinEd interventions. Surveys will be distributed electronically via REDCap or by mail, with a pre-stamped, pre-addressed return envelope, according to their preferences. Non-responders of the survey will be approached to complete the survey via phone or in the clinic. Patients will be sent $30 and $40 gift cards after completion of the 3- and 6-month surveys, respectively.

### Sleep study procedures

3.9

Participants may opt to take part in an optional sleep monitoring sub study, which involves objective assessment of sleep quality using wrist actigraphy (Ambulatory monitoring inc., Ardsley, NY)—a noninvasive, ecologically valid method widely used to measure sleep-wake patterns [[44], [45], [46]]. Wrist actigraphy has been validated against electroencephalogram (EEG) measures and shows strong agreement with polysomnography, with correlations exceeding 90% in adults [[44], [45], [46]].

Interested participants will be asked to wear an actigraph on their non-dominant wrist continuously (24 h/day) for 7 consecutive days at three time points: within 3 weeks of enrollment, and at 3- and 6-months post-randomization, in accordance with standard recommendations [44]. Participants will begin actigraphy monitoring before receiving study intervention at any time. To support accurate data interpretation, participants will also complete a daily actigraphy log during each 7-day monitoring period. The log will capture the time the participant got into bed, the time they attempted to fall asleep, the time of final awakening in the morning, the time they got out of bed for the day, the timing and duration of any daytime naps, periods when the actigraph was removed or reattached, and any unusual events that could affect sleep or wake patterns (e.g., illness, travel, or prolonged sedentary activity).

The actigraphy kit—including the device, an instructional guide, a cover letter, and a pre-stamped, pre-addressed return envelope—will be mailed to participants by the study team.

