#### FinEd

3.7.2

Patients will receive FinEd intervention within 4 weeks after enrollment. The intervention consists of mailing patients a packet including: (1) a comprehensive list of local resources that can help with food insecurity, transportation or living expenses; (2) contact information for national non-profit financial navigation organizations such as Patient Advocate Foundation where patients can self-refer. PAF provides case management and financial aid assistance to individuals facing chronic, life-threatening, and debilitating illnesses. [41], and (3) financial education materials in the format of brochures and videos with QR codes on topics such as understanding health insurance costs, how to read an explanation of benefits and medical bills, how to find care that is covered by insurance, how to use price estimator tool (brochure only), choosing a health plan (brochure only). The videos are developed by our research team using content from publicly available materials and input from a team of patients, patient educators, and community advisors working with our cancer center community outreach engagement team. After delivery of the intervention materials, a bilingual study coordinator will set up a one-time phone or zoom meeting with the participants to give an overview of resources shared, and answer patients’ questions. The study coordinator will complete a study-specific training under supervisor of a senior researcher on how to discuss the resources to ensure fidelity in delivery of intervention.

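### The 7-day baseline actigraphy must only begin, not finish, before the intervention, so 1 to 6 baseline nights may follow first contact in FinEd and CostCOM but not in EUC

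*Protocol article*

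**What the plan says.** Section 3.9 describes a voluntary component ("Participants may opt to take part in an optional sleep monitoring sub study") in which a wrist actigraph is worn "for 7 consecutive days at three time points: within 3 weeks of enrollment, and at 3- and 6-months post-randomization". The device is not handed over in clinic; the kit "will be mailed to participants by the study team". The only ordering rule is "Participants will begin actigraphy monitoring before receiving study intervention at any time". No sentence says that the 7 days must be over by then.

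The intervention timings stand elsewhere:

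- **FinEd (3.7.2):** "Patients will receive FinEd intervention within 4 weeks after enrollment". Delivery is a mailed packet, followed by one call with a coordinator.
- **CostCOM (3.7.3):** two statements. The intervention is received "within 4 weeks of enrollment", and "Sessions take place by phone or video at enrollment and 3 months post-randomization".
- **EUC (3.7.1):** study-specific identification of need only, with no packet or session.

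Objectively measured sleep is among the secondary outcomes in section 2, and Table 1 gives it four actigraphy rows.

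**The concern.** A baseline recording serves as a baseline only if it precedes the intervention. A rule that protects just the first day of a week-long recording does not secure that. Overlap would not need a protocol deviation; it could arise in ordinary compliance.

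The exposure is also uneven. FinEd and CostCOM participants can have contact during the baseline week, while EUC participants have nothing to be contacted about. Any distortion would therefore enter the comparisons that section 3.12.3 plans, each intervention arm against EUC, and would not cancel between arms.

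The two CostCOM timings add a second difficulty. If the first session really takes place at enrollment, a participant who waits for a mailed device cannot have started wearing it beforehand.

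**Working it through.** The plan gives no figure on this point. Its only computed precision figures, the confidence limits in Table 2, concern the primary outcome and do not enter here. The check is a comparison of the stated windows.

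**Inputs**, in whole days with enrollment as day 0:

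| Quantity | Value | Source |
|---|---|---|
| Length of recording | 7 consecutive days | 3.9 |
| Start day *s* of the baseline recording | 0 to 21 if the 3-week window limits the start; 0 to 14 if it limits completion (the text does not say which) | 3.9 |
| Day *t* of first intervention contact | 0 to 28 | 3.7.2, 3.7.3 |
| Ordering rule | *s* < *t* (a same-day start is counted as a breach) | 3.9 |

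**Step 1. How many nights can follow contact?** If contact falls on day *t* = *s* + *k*, then *k* nights precede it and 7 − *k* follow it:

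| *k* | Nights after contact | Share of the week |
|---|---|---|
| 1 | 6 | 86% |
| 2 | 5 | 71% |
| 3 | 4 | 57% |
| 4 | 3 | 43% |
| 5 | 2 | 29% |
| 6 | 1 | 14% |
| 7 or more | 0 | 0% |

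All rows satisfy *s* < *t*, so all are allowed.

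**Step 2. Is overlap a corner case of the rule?** Count the whole-day pairs (*s*, *t*) that obey it.

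- Window limits the start: compliant pairs = Σ(28 − *s*) for *s* = 0 to 21 = 616 − 231 = 385. Overlapping pairs = 22 × 6 = 132.
- Window limits completion: compliant pairs = Σ(28 − *s*) for *s* = 0 to 14 = 420 − 105 = 315. Overlapping pairs = 15 × 6 = 90.

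These are counts of possible schedules, not probabilities. They show only that overlap fits easily within the rule.

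**Step 3. Could the rule be tightened within the stated windows?** Require *t* ≥ *s* + 7. Under the first reading, the latest start is day 21 and 21 + 7 = 28, the 4-week limit. Under the second, the latest start is day 14 and 14 + 7 = 21, a week before the limit. A clean baseline is feasible under both readings, and no night then follows contact.

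**Step 4. The CostCOM session at enrollment.** Put *t* = 0. The rule *s* < *t* then needs *s* < 0, a start before enrollment. The window in 3.9 runs from enrollment onward, so no start day complies. On a literal reading, sections 3.7.3 and 3.9 cannot both be followed, and 3.7.3 also disagrees with its own 4-week window.

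**The case against.** The staggered windows, 3 weeks for actigraphy and 4 for the intervention, leave room for a complete week first. Read as a limit on completion, the 3-week window leaves a further week to spare. This stands as to feasibility, and for that reason no claim is made that the windows are too tight. But room for a clean baseline is not a requirement for one.

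The phrase about a session at enrollment may be no more than a label separating the first session from the one at 3 months. That is plausible, and it makes the conflict one of wording. The sections still have to be reconciled.

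The scope is small: an optional sub-study in a 90-patient pilot that reports descriptive estimates. The primary outcome is untouched, and the baseline Insomnia Severity Index belongs to a survey completed before randomization (3.5, 3.6). This stands and limits the weight of the point.

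A reader might infer three stronger claims, none of which the documents support:

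- *The baseline week may lie wholly after the intervention.* The ordering sentence forbids a start after contact. That case arises only from the literal CostCOM conflict, and section 3.7.2 has no such statement for FinEd.
- *Patients choose the sub-study after learning their arm.* The article does not say when opt-in occurs. Consent comes before the baseline survey and randomization, and the optional interviews in 3.10 are consented to at enrollment. Silence here is detail that a condensed article may leave to the full protocol.
- *A known share of the effect, or a number of minutes of sleep, is lost.* That would need an immediate, constant effect on sleep and an analysis of change from baseline. The documents give no early effect, and section 3.11.2 specifies change from baseline for the patient-reported measures but only lists the actigraphy parameters.

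**Conclusion.** The concern holds in a limited form. As written, section 3.9 lets 1 to 6 of the 7 baseline nights (14% to 86%) follow first intervention contact in FinEd and CostCOM, with no counterpart in EUC. This rests on the plain wording of the ordering sentence and on whole-day counting. It does not depend on which reading of the 3-week window is taken. The percentages are shares of nights, not of any treatment effect; the size and direction of bias in objective sleep cannot be computed from the documents, nor can the number of participants affected.

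The two CostCOM timings in section 3.7.3 are a separate inconsistency, with each other and, if enrollment is taken literally, with section 3.9.

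This is a worthwhile low-cost improvement to a stated procedure, not a threat to the trial's main result.

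**What to change.** 1. In section 3.9, require the 7-day baseline recording to be *completed* before first intervention contact, with contact defined as the packet or a session, whichever comes first. State whether the 3-week window limits the start or the completion of wear.
2. Reconcile section 3.7.3 with itself and with section 3.9 on the first CostCOM session. Which timing applies is for the investigators to settle.
3. Record contact dates in the study database, and flag any baseline nights after contact in a sensitivity analysis. The daily actigraphy log will not do this alone, because its listed contents do not include intervention contact. For FinEd the packet goes by mail and the article describes no receipt date, so the study should fix which date counts. Flagging is preferable to dropping nights from the main analysis, which would shorten baselines in the active arms only.

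The cost is a few words of protocol text, a recorded date and a date check. The practical downside is that, for some sub-study patients, contact must be booked after the recording ends. If the 3-week window limits the start, a recording begun on day 21 leaves only day 28 for contact.

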### Qualitative interviews

3.10

We will conduct one-on-one qualitative interviews with 5 participants from the FinEd arm who consented to these interviews at the enrollment. This sample size was selected based on availability of funding and resources to refine the intervention prior to larger-scale evaluation. Selection of participants will be purposeful based on participants' responses to follow-up surveys indicating use of FinEd intervention materials. These interviews will be conducted via phone or video to assess participants' experiences and satisfaction with the FinEd intervention. Each interview is expected to last approximately 30–45 min. Participants with a completed interview will receive a $40 gift card. Given our team have previously conducted qualitative interviews with patients receiving the CostCOM intervention [22], we will not interview any patients from this arm.

### Patient assessments

3.11

#### Primary efficacy outcomes

3.11.1

The primary outcome is patient-reported cost-related cancer care nonadherence within 6 months post-randomization. Cost-related cancer care nonadherence is defined as a positive response to any of the following: (1) delay, (2) forego, (3) stop, or (4) change in cancer prescribed medication due to cost, (5) refuse recommended cancer tests, or (6) skip cancer office visits due to cost, adapted from Medical Expenditure Panel Survey [34]. At each of the 3-, and 6-month follow-ups, patients will be asked about the presence of nonadherence (yes/no) since the last follow-up. Cost-related cancer care nonadherence at 6 months will be calculated as a report of nonadherence at any of the 3 and 6-month follow-ups (yes/no). We will also evaluate the presence of cost-related cancer care non-adherence at each time point separately.

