**Method:**

We propose a three-arm pilot randomized controlled trial comparing FinEd, enhanced usual care (EUC) and CostCOM in 90 newly diagnosed cancer patients undergoing systemic or radiation therapy who screen positive for financial hardship or HRSNs. FinEd includes (1) a list of local/national resources for financial and HRSNs support, and (2) educational materials on health insurance, delivered via mail and a one-time phone/video session with a study coordinator. CostCOM includes (1) systemic therapy OOPC estimates, (2) financial navigation to identify assistance programs, and (3) financial counseling, delivered over two phone/video sessions by a financial navigator. EUC includes study-specific identification of financial hardship and HRSNs. Our goals are to investigate preliminary efficacy of the three arms within six months post-randomization on cost-related care non-adherence (primary outcome), treatment completion, missed appointments, financial worry, material hardship, insurance literacy, quality of life, and sleep quality. We will evaluate patient experience with FinEd using qualitative interviews.

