The CAN-ASSIST trial is a three-arm pilot randomized controlled trial testing the preliminary efficacy of navigator-free financial education and resources (FinEd) vs. enhanced usual care (EUC) vs. out-of-pocket cost communication and financial navigation (CostCOM) on domains of financial hardship (care non-adherence, material hardship, and financial worry), financial health literacy, quality of life, and sleep quality among cancer patients on systemic treatment who screen positive for financial hardship and HRSNs [15].

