### Eligibility criteria

3.3

Patients with the following characteristics are eligible for the study: 1) Age of 18 years or older, 2) being able to answer surveys and interact with the study team in English or Spanish, 3) a new cancer diagnosis of any type or stage by histology in the last 120 days, 4) having started systemic cancer treatment or radiation therapy, 5) being treated in our cancer center oncology clinics, 6) screen positive for financial hardship or HRSNs (see Section 3.4). The 120-day window was selected because prior research shows patients prefer early financial screening [27]. Financial hardship peaks in the first few months after early-stage cancer diagnosis and improves thereafter, [28,29], whereas it worsens over time in metastatic cancer [30], thereby justifying the use of 120 days since diagnosis as an inclusion criterion.

The exclusion criteria included Eastern Cooperative Oncology group (ECOG) performance status more than 2, participation in other therapeutic clinical trials that cover the cost of treatment, prior history of cancer diagnosis or treatment in the last 24 month except for in situ cancers, non-melanoma skin cancers, and breast cancers diagnosed more than 24 months ago who were only receiving hormonal treatment in the last 24 months.

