#### Secondary efficacy outcomes

3.11.2

Secondary outcomes and their definitions are shown in Table 1 and include treatment completion [47] (yes/no), rate of missed appointments [47], and material financial hardship [34] within 6 months post randomization, as well as changes in patient-reported financial worry [31,32], health insurance literacy [43], QOL [35], subjective sleep quality [37] between baseline and 3- and 6-months. A sleep quality parameters will be calculated using the Action-W program and include: sleep duration (total nighttime sleep minutes), sleep efficiency (ratio of nighttime sleep duration to total sleep period), sleep latency (minutes to first sleep epoch), and sleep fragmentation (ratio of number of nighttime awakenings to nighttime sleep duration ∗ 100). The index of sleep fragmentation considers movements of varying intensity [43].

**Table 1 tbl1:** Preliminary Efficacy Outcome Measures and co-variates.

Outcome	Definition	Source
Cost-related cancer care nonadherence *(****Primary)***	Any incidence during the 6 months (measured at 3, and 6 months) when a patient self-reports a positive response to any of: (1) delay, (2) forego, (3) stop, or (4) change in cancer prescribed medication due to cost, (5) refuse recommended cancer tests, or (6) skip cancer office visits due to cost (adapted from Medical Expenditure Panel Survey) [34]. The outcome will be binary (yes/no).	Patient surveys at 3& 6 months. Outcome will also be measured at baseline to control baseline data.
Treatment completion	Receipt of the prescribed cycle of chemotherapy and/or radiation therapy due within the 6-month study period, determined by EMR abstraction (Yes/No) [47]. Patients with treatment interruptions/stoppages because of toxicities, other medical reasons, facility factors, or death will be considered as having completed treatment if they complete all recommended treatment within the 6-month interval. Treatment interruptions/stoppages without medical reasons will be considered incomplete treatment.	EMR
Missed appointment	Proportion of outpatient medical or radiation oncology treatment appointments (including infusion) or office visits (including tele medicine) that is marked as cancellation or no shows and are provider-initiated or are not due to scheduling errors [47]	EMR

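### Patients on radiation alone are eligible, but no primary-outcome item names radiation, so cost-related delay, refusal or stopping of radiation is not reliably captured

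*Protocol article*

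**What the plan says.** **Who can enter.** The fourth criterion in section 3.3 (Eligibility criteria) is "having started systemic cancer treatment or radiation therapy". The Abstract agrees: "90 newly diagnosed cancer patients undergoing systemic or radiation therapy who screen positive for financial hardship or HRSNs". Radiation alone is enough. The last paragraph of the Introduction is narrower and describes the trial as running "among cancer patients on systemic treatment who screen positive for financial hardship and HRSNs".

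**What the primary outcome counts.** Section 3.11.1 scores a patient as nonadherent on a positive answer to any of six items. Items 1–4 are "1) delay, (2) forego, (3) stop, or (4) change in cancer prescribed medication due to cost". Items 5 and 6 are "5) refuse recommended cancer tests, or (6) skip cancer office visits due to cost". Table 1 gives the same list, introduced by "Any incidence during the 6 months (measured at 3, and 6 months) when a patient self-reports a positive response to any of". Neither place mentions radiation or cancer treatment in general.

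**What the secondary outcomes count.** Table 1 does name radiation for treatment completion: "Receipt of the prescribed cycle of chemotherapy and/or radiation therapy due within the 6-month study period, determined by EMR abstraction". Its definition of missed appointments also covers radiation oncology, and lists treatment appointments separately from office visits.

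**The concern.** The trial aims to measure care that patients give up because of cost. For a patient treated with radiation alone, the main care that could be given up is the radiation course, and no item asks about it directly. A patient who delays, declines or stops radiation because of cost, but keeps tests and office visits, can answer no to all six items and be scored as adherent. The item set fits the population described in the Introduction better than the one that section 3.3 admits.

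Any event missed this way lowers the measured rate. If it happens similarly in all arms, it also shrinks the absolute difference between them. Randomization is stratified by stage only (section 3.6), so the radiation-only share can differ between arms by chance. The pilot's estimates are meant to inform a larger trial, and a gap in the outcome definition could carry over into its planning.

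**Working it through.** **1. Coverage of the six items**

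| Item | Object of the item | Names radiation? |
|---|---|---|
| 1–4: delay, forego, stop, change | prescribed cancer medication | no |
| 5: refuse | cancer tests | no |
| 6: skip | cancer office visits | no, but a patient may read it to include radiation sessions |

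Table 1's own wording elsewhere shows that the authors name radiation when they mean it, and that they treat treatment appointments and office visits as different things.

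**2. The plan's own figure.** Section 3.12.1 and Table 2 use n = 30 per arm. The one-sided Clopper-Pearson upper limit is the Beta quantile at the confidence level, with parameters x + 1 and n − x, where x = nP. For P = 0.05, x = 30 × 0.05 = 1.5, and the 95% quantile of Beta(2.5, 28.5) is 0.17251, which matches the plan. All nine cells of Table 2 reproduce. The precision figures are correct, and this point does not depend on them.

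**3. Scale of the events.** Table 2's range implies 30 × 0.05 = 1.5 to 30 × 0.15 = 4.5 events per arm. One event is 1/30 = 3.3 percentage points.

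**4. Possible loss.** The documents give neither the radiation-only share r nor the fraction m of these patients' events that the items miss. Assumptions: r = 10–30%, m = 50–100%, and the same true rate P in radiation-only patients as in the others. Then:

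- observed rate = P × (1 − r × m)
- expected missed events per arm = 30 × P × r × m

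The product r × m runs from 0.10 × 0.5 = 0.05 to 0.30 × 1 = 0.30.

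| True P | Observed rate | Missed events per arm | 95% upper limit (Table 2 value) |
|---|---|---|---|
| 0.05 | 0.035–0.0475 | 0.075–0.45 | 0.151–0.169 (0.1725) |
| 0.10 | 0.07–0.095 | 0.15–0.90 | 0.200–0.232 (0.2386) |
| 0.15 | 0.105–0.1425 | 0.225–1.35 | 0.245–0.291 (0.2995) |

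If r and m are equal in two arms, the absolute difference between them is multiplied by the same factor, 1 − r × m, which is 0.70 to 0.95.

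**The case against.** The strongest reply is that radiation is given at appointments. A patient who abandons it because of cost stops attending and may well endorse item 6. Table 1's separation of treatment appointments from office visits is a rule for abstracting records and does not show how patients read a survey question. The survey text itself is not shown. This stands in part: item 6 is a partial safeguard. It is not a dependable one, because the definition does not say that radiation sessions count as office visits, and a patient can stop a course yet still attend visits.

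A second reply is that radiation stoppages are visible elsewhere, through treatment completion and missed appointments. That is true, but both come from the medical record and neither is specific to cost, so they cannot correct a patient-reported, cost-related outcome. Cancer treatment is also a listed covariate, and section 3.12.3 plans logistic regression. Adjustment can address imbalance, within the limits of few events, but it cannot recover events that were never recorded.

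A reader might infer more than the documents support:

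- *Every radiation-only patient who stops because of cost is scored as adherent.* Item 6 may catch some of them.
- *Items 1–4 do not apply to radiation-only patients at all.* Nothing in the article says that these patients have no other cancer prescriptions.
- *Nonadherence is certainly understated in every arm.* That requires such events to occur and to be missed.
- *The loss is about two thirds of the anticipated rate* (3.3 points against 5%). That sets one whole missed event against the lowest rate in Table 2. The expected loss at 5% is 0.075 to 0.45 events per arm.

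**Conclusion.** The point holds as a gap in coverage. The primary outcome is fully stated in two places, and in both it omits a treatment that qualifies patients for entry. Cost-related delay, refusal or stopping of radiation is therefore not reliably captured. This is a matter of what the definition says, and not of detail left to another document.

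The direction is clear: a missed event can only lower the measured rate. The size is not known. Under the stated assumptions the expected loss is about 0.1 to 1.35 events per arm across Table 2's range. At the anticipated 5% it is less than half an event, which is small beside the sampling uncertainty at 30 per arm. The case for acting is that the correction is cheap and the definition may be reused in the larger trial. The documents do not show that the pilot's estimates would be seriously distorted.

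**What to change.** Extend the primary outcome to radiation in section 3.11.1, in Table 1 and in the English and Spanish surveys:

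- **If no surveys have been collected:** word items 1–4 as *cancer medication or radiation treatment*, including in the baseline version.
- **If surveys have been collected:** leave the six existing items unchanged and add one separate item on cost-related delay, refusal or stopping of radiation. Report the outcome with and without that item, and also in patients receiving systemic therapy.

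Reconcile the population in the last paragraph of the Introduction with the Abstract and section 3.3.

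The cost is a survey amendment in two languages and a few extra rows in the results. It is also a small further departure from an instrument already described as adapted. If the change comes midway, earlier participants will have no answer to the radiation item. Rewording items 1–4 at that stage would be worse, because it would mix two versions of the primary outcome and could separate a patient's baseline from follow-up.
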